### Structured education programme plus follow on support (Walking Away Plus)

Participants receive the same advice leaflet, Walking Away structured group education programme and annual maintenance sessions. In addition they are introduced and given access to a highly tailored text-messaging follow-on service designed to support behaviour change and pedometer use with additional telephone calls from educators that are initiated after attendance at the Walking Away programme. Details of the text messaging and telephone follow-on support service are detailed in Table 3 and have been submitted for publication elsewhere. In brief, approximately one week after the Walking Away session, an educator telephones the participant to help them identify a short- and long-term step goal and action plan for the next six months, and to elicit information on tailoring variables including confidence in increasing physical activity, previous experience of physical activity and potential mobility issues that prevent walking being the primary activity. The educator records the information in an online form and saves it on a database for use by the text-messaging programme. A key feature of the text-messaging and pedometer support is that participants are prompted to text in their weekly step count. They then receive automated feedback by text message tailored to the extent to which they achieved their goals, in relation to the tailoring variables. Participants also receive text-messages using evidence-based behaviour change techniques and a six month telephone call to review their goals and action plans, prompt problem solving and provide social support. The key techniques used in the follow-on support are goal setting (behaviour), action planning, self-monitoring, goal review, problem-solving and social support [43]. The intensity of the ‘follow-on support’ varies over the course of the year (see Table 3) and is repeated over the four years of the study. Participants who do not wish to receive text-messages can opt out at any time.

**Table 3 Tab3:** ‘Follow on’ support for the Walking Away Plus Group, repeated over the four years of intervention

Time point from education attendance	Type of contact and frequency	Content (behaviour change techniques and their delivery)
0 months	First group session (3 hrs)	• As the ‘Walking Away’ group plus extra 15–20 minutes at end of the session to explain the follow-on support and what to expect over the next 12 months in terms of text-messaging, pedometer support and telephone calls.
		• One week of self-monitoring (using the pedometer and activity diary) and text messages prompting participant to ‘text in’ their weekly step total at the end of the week (‘baseline’ steps).
1 week	First telephone call from educator (15 minutes)	• Educator prompts participant to set an action plan and personal short term and long term goals informed by the baseline steps, and asks participant about their confidence to achieve goals and previous levels of physical activity. Educator records this information on an online form which saves to a database for use in tailoring subsequent text-messages.
0-2 months	Text message contact (1–3 per week)	• Participant monitors activity (pedometer step counts) each week, using a pedometer, an activity diary and a converter to translate activities other than walking into steps.
		• Participant receives text-messages asking them to ‘text in’ weekly step count total.
		• Participant receives feedback by text-message tailored to goal achievement, confidence, and previous physical activity levels.
		• Participants who do not make progress with goals receive ‘problem solving’ texts, asking them to text in barriers, followed by tailored replies.
2-6 months	Text message contact (one per week)	• Weekly tailored messages targeting attitudes and beliefs, motivation, self-efficacy and self-regulation of PA behaviours.
		• Participant is asked to self-monitor and record steps for 1 week and text in weekly amount (ahead of 6 month telephone call)
6 months	Telephone contact; 15 minutes	• Educator gives feedback on goal progress, and reviews goals.
		• Educator prompts problem solving in relation to barriers.
		• Educator identifies and highlights benefits experienced.
		• Educator discusses whether experiences of behaviour change are satisfying and reinforcing.
		• Educator provides social support.
		• Educator prompts continued goal setting and action planning.
7-12 months	Text message contact once per month	• Monthly tailored messages target attitudes and beliefs, motivation, self-efficacy and self-regulation of physical activity behaviours.
		• Participant is asked to self-monitor and record steps for 1 week and text in weekly amount (ahead of 12 month group education session)
OPTIONAL	Telephone contact; 15 minutes	• Educators call participants who do not respond to text requests for step counts, to encourage participation and solve any problems.
12 months	Walking Away maintenance session; 2.5 hours	• See Walking Away group (Table 2).

This annual structure is repeated each year following each group education maintenance session for the 4 year intervention period

### Educator recruitment, training and quality assurance (intervention fidelity)

Educators can be registered health care professionals (e.g. nurse, dietician) or a suitable non-registered professional (e.g. Health Trainer). Across the study sites, 16 educators have been recruited from a range of registered and non-registered Health Care Professionals from local healthcare providers and other appropriate settings. This mix of personnel was included in order to make the study as pragmatic and generalisable as possible to routine health care systems. To ensure that all interventions are delivered by educators as planned, a fidelity standard operating procedure has been put in place. All educators attended an initial two day training course to ensure that they understood the theories and philosophy that underpin the Walking Away programme and the content and resources used within it. All educators were given a written curriculum to support their delivery of the programme and given the opportunity to practise delivery of the programme. Quality assurance of delivery is undertaken to assess educational style and content using established tools used within routine care through the DESMOND Collaborative [44]. Educators receive structured and instructive feedback from their assessor and key goals and action plans are developed in order to help them improve their performance. Prior to the delivery of the one year intervention, educators received training to be able to deliver the Walking Away Maintenance session which is also supported by a written curriculum.

Educators attended additional training in delivering the telephone calls to participants in the ‘Walking Away Plus’ group. The training was supported by an extensive curriculum outlining the contents (behaviour change techniques, patient-centred communication skills) and mode of delivery of the follow-on support. The curriculum also contains standardised scripts that educators are asked to follow, an explanation of the intervention fidelity procedures, and standardised reflection sheets and checklists to promote and assess fidelity of the phone calls. Educators are asked to audio-record the telephone calls, listen back to a sample, complete the checklists, and discuss these with the intervention lead. The number of calls assessed and their frequency depends on the competence level of the individual educators as well as the year of intervention delivery. Monitoring the delivery of the text-messaging system is done on a weekly basis by examining automatically generated lists of messages sent and received.

### Study outcomes

Data collection clinics are run by research nurses in the Leicester Diabetes Centre, the MRC Epidemiology Unit, Cambridge and other local community centres and clinic areas. All staff have been trained in study procedures and data are collected following standardised operating procedures. Written informed consent is obtained from all participants prior to the commencement of data collection. Details of all clinical assessments and outcome measures are provided in Table 4. Participants are sent a letter with details of selected clinical results after each visit, and their results are also sent to their general practitioner.

**Table 4 Tab4:** Participant assessments at each time point

Clinical Assessment	0 months	12 month	48 months
Family history of disease	X	X	X
Medication status	X	X	X
Smoking status	X	X	X
Muscular/skeletal injury	X	X	X
Blood pressure*	X	X	X
Height*	X		X
Weight*	X	X	X
Waist circumference*	X	X	X
Arm and leg length	X		
Body fat percentage	X	X	X
Fasting and 2-hr glucose and insulin (Leicester only)	X	X	X
HbA_1c_*	X	X	X
Lipids*	X	X	X
Urea & Electrolytes*	X	X	X
Liver Function Tests*	X	X	X
7 Day Step Count & Physical Activity (accelerometer)	X	X	X
Recent Physical Activity Questionnaire (RPAQ)	X	X	X
Dietary questions	X	X	X
Brief Illness Perceptions Questionnaire (BIPQ)		X	X
Physical activity self-efficacy	X	X	X
Enactment of techniques (Groups 2 & 3 only)		X	X
EQ-5D; SF-8	X	X	X
Hospital Anxiety and Depression Scale (HADS)	X	X	X
Sleep	X	X	X
Neighbourhood Environment Walkability Survey (NEWS)	X		
Use of health resources	X	X	X

*Results of these assessments are sent to the participant and their primary care physician

### Primary outcome

The primary outcome measure is change in ambulatory activity (steps per day) at 48 months, assessed by accelerometer (Actigraph GT3X+) with an intermediary assessment at 12 months. Participants are asked to wear the accelerometer on a waistband (in the right anterior axillary line) for seven consecutive days during waking hours following their baseline and follow-up visits. In addition, participants are asked to fill in a log sheet each day that they wear the accelerometer indicating time the accelerometer was taken off at night, time they went to sleep, time they woke up and time the accelerometer was attached. At the end the seven days of wear, participants are asked to return the accelerometer and the log sheet to the research team in a pre-paid envelope. Raw acceleration data are captured and stored at 100 Hz. Data processing will be undertaken on commercially available analysis tools. At least three days valid wear is required to count as a valid recording. Non-wear time is determined by one hour or more of consecutive zero counts. Due to the potential for bias between groups in factors used to acquire valid accelerometer data, average wear time and the number of valid days will be included as covariates in the analysis.

### Secondary outcomes

#### Accelerometer

The accelerometer used to measure the primary outcome, detailed above, is also used to assess the number of censored steps taken per day, defined as steps taken above an intensity used to distinguish between purposeful and incidental ambulation [45]. In addition, commonly used cut-points will be used to distinguish between time spent sedentary and in time spent in light-, moderate, and vigorous-intensity physical activity [46]. We will also use this data to assess compliance to the physical activity recommendation of undertaking at least 150 minutes of moderate-to-vigorous intensity physical activity per week in bouts of at least 10 minutes.

#### Time spent lying, standing, sitting and postural transitions

Participants are also asked to wear an activPAL3™ device for the same seven days as the ActiGraph accelerometer. This is a small slim thigh worn monitor that uses accelerometer-derived information about thigh position to determine body posture (i.e., sitting/lying, standing and stepping). The activPAL3™ is initialised using manufacturer’s software with the default settings (i.e., 20Hz, 10s minimum sitting-upright period) and participants are asked to wear the device continuously (24 hours/day). The device is covered with a nitrile sleeve and fully wrapped in one piece of waterproof dressing (Hypafix Transparent) to allow participants to wear the device during bathing activities. The activPAL3™ is worn on the midline anterior aspect of the upper thigh and secured using hypoallergenic waterproof dressing (Hypafix Transparent).

#### Recent Physical Activity Questionnaire (RPAQ)

Self-reported physical activity is measured using the RPAQ. This assesses physical activity across four domains (domestic, recreational, work, commuting) over the previous month. The domestic section contains questions regarding computer use, TV-viewing and stair climbing at home. The questions in the recreational domain ask about frequently performed activities, including frequency and duration. The work domain examines the level of physical activity associated with their current employment, and commuting assesses four modes of usual transport: walking, cycling, car, and public transport. It has shown moderate-to-high reliability for physical activity energy expenditure, and good validity for ranking individuals according to their time spent in vigorous intensity physical activity and overall physical activity energy expenditure [47]. Participants also complete the Neighbourhood Environment Walkability Survey (NEWS) which captures the environmental context in which participants live and will be used to assess environmental determinants of physical activity and physical activity behaviour change [48, 49].

#### Biochemical variables

Standard biomedical outcomes are assessed by venous sampling. These consist of HbA1c, lipid profile (triglycerides, HDL, LDL, total cholesterol), urea and electrolytes (sodium, potassium, urea, creatinine) and liver function tests (albumin, total bilirubin, alkaline phosphatase, alanine transaminase).

At the Leicester site only, participants are assessed for fasting and 2-hour post challenge glucose and insulin levels using an Oral Glucose Tolerance Test (OGTT). The OGTT results will be used to provide greater clinical insight into how the promotion of physical activity affects metabolic health in prediabetes, given 2-hour glucose and insulin levels better reflect peripheral insulin sensitivity. Given that the new WHO guidelines [40] have led to local clinical practice basing diagnosis of T2DM on HbA_1c_ criteria, the routine use of the OGTT has been phased out of primary care. Therefore, in order to comply with local guidelines and to avoid confusing clinical management strategies in recruited practices, OGTT samples taken in Leicester are frozen and will be analysed after the final study visit (48 month) and not form part of a diagnosis of diabetes. The OGTT involves a fasting blood sample being taken from the patient before they are then given a glucose load of 75 g. A second sample is taken 2 hours later. Fasting and 2-hour plasma glucose and insulin samples are taken at each clinical visit and stored in a −80 °C freezer using standardised, stable methodology within the Leicester Diabetes Research Centre.

#### Genetics

A blood sample for genetic analysis is also collected in those who provide their consent. The aim of this sample will be to investigate group level associations and interactions of physical activity, obesity and genes in the development of T2DM. The genetic assessments will be focused on genes for which there are biological plausibility for interaction.

#### Anthropometric and demographic variables

Body weight, body fat percentage, height and waist circumference are measured to the nearest 0.1 kg, 0.5 %, 0.5 cm and 0.1 cm respectively. Waist circumference is measured using a soft tape mid-way between the lowest rib and iliac crest. Arterial blood pressure is obtained from the right arm of the seated participant. Three measurements are taken and an average of the last two measurements will be used. Total upper arm length, forearm length, total leg length and lower leg length are measured on the left side of the body. Information on ethnicity, medication history, current smoking status, family history of diabetes in first and second degree relatives, and muscular/skeletal injury that prevents physical activity are obtained by self-report.

#### Cardiovascular risk

Cardiovascular risk is calculated using the Framingham risk calculator.

#### Self-reported dietary behaviour

In order to capture dietary behaviour, two short questionnaires used in previous research studies by our group are administered to the participants for self-completion. These questions are based on dietary questionnaires developed for the EPIC (European Prospective Investigation of Cancer and Nutrition) study and the international NAVIGATOR (Nateglinide And Valsartan in Impaired Glucose Tolerance Outcomes Research) study [50, 51].

#### Sleep

Participants self-report on two questions concerning sleep duration over the past 24 hours and over a usual week. There is accumulating evidence for an association between short sleep duration (<6 hours per 24 hours) and long sleep duration (≥10 hours per 24 hours) and metabolic dysfunction [52].

#### Health related quality of life

Health related quality of life data is measured using the European Quality of Life-5 Dimensions (EQ-5D) [53] and the Short Form (SF-8) Health Survey [54]. The EQ-5D is a standardized questionnaire that was developed for use as a measure of health outcomes and defines health in terms of five dimensions: mobility, self-care, usual activities, pain or discomfort, and anxiety or depression. It is widely used to calculate ‘quality adjusted life years’ (QALYs) which are essential to cost-effectiveness analysis. The SF-8 is a self-administered questionnaire measuring eight health domains (general health, physical functioning, role physical, bodily pain, vitality, social functioning, mental health and emotional roles) with eight questions. The standard (4 week) recall format will be used. Data from SF-8 is represented as a physical component score and a mental component score.

#### Depression and anxiety

Depression and anxiety are measured using the Hospital Anxiety and Depression (HADS) Scale, to produce independent subscales for anxiety and depression [55].

#### Health resources

A health resources questionnaire records the number of times over the past 12 months that the participant has seen a health care practitioner such as a GP, nurse or other health workers, and the number of times they have been to hospital. In addition, the contact and costs associated with the intervention will be captured by the research team. These costs will be inputted into the cost effectiveness analysis of the intervention.

### Process measures

#### Perceptions of diabetes risk

Perceptions and perceived knowledge of diabetes risk is measured at 12 and 48 months using the validated Brief Illness Perceptions Questionnaire (BIPQ) [56]. This eight item instrument uses an 11 point Likert scale (0 = no effect, 10 = complete effect) to measure five cognitive diabetes risk representations (consequences, timeline, personal control, treatment control, and identity), two emotional representations (concern and emotion) and risk comprehensibility (perceived knowledge).

#### Self-efficacy in relation to physical activity

Self-efficacy is measured at baseline, 12 and 48 months. Six items measure participants’ confidence in their ability to undertake any form of moderate- to vigorous-intensity physical activity for 10 minute periods, increasing incrementally from 10 minutes to one hour each day. Items use a 100 % confidence rating scale (where 0 % = no confidence, and 100 % represents complete confidence). An overall score is calculated by summing the efficacy scores for each time period and dividing by the number of time periods.

#### Enactment of the behaviour change techniques

Participants’ use of behaviour change techniques included in the Walking Away and Walking Away Plus groups is assessed at 12 and 48 months. A 5-point Likert scale (where 1 = most of the time and 5 = never) assesses how often participants set goals, form action plans, use a pedometer, complete an physical activity log, are aware of their activity levels, and are trying to be more physically active.

#### Uptake and adherence to Walking Away and Walking Away Plus interventions

Measures of uptake and adherence to the intervention groups will include: 1) group session attendance to Walking Away, 2) group session attendance to the annual maintenance sessions at 12, 24 and 36 months 3) proportion of phone calls completed, 4) number of participants who registered for the text messaging service, 5) number of STOP messages received for test messaging (i.e. number opting out of the text messaging and pedometer support), 6) proportion of intended texts sent, and 7) number of step count texts received from participants relative to the number of requests they are sent (engagement).

### Qualitative process evaluation

A process evaluation will be conducted using a combination of ethnographic methods including observations of education sessions and individual interviews. Briefly, we will observe a sample of Walking Away sessions and undertake interviews with a sample of participants from all three trial groups. Analysis will be informed by the constant comparative method; the focus will be exploring whether and how participants engage with each component of the intervention(s).

### Sample size

#### Primary outcome

For 1-beta = 0.8, alpha = 0.025 (allowing for 2 a priori comparisons against control conditions), SD = 4000 steps/day and a drop-out of 30 %, we require 436 per group (1308 in total) to detect a 1000 steps/day difference in change in ambulatory activity (equivalent to 10 mins walking/day or 70 mins walking/week) between the intervention groups and control group. Assuming 25 % of participants in the total cohort are SA we have an 80 % power to detect around a 2000 steps/day difference when comparing two intervention comparisons to the control group (alpha = 0.025) in the SA population.

Several intervention studies with a follow-up of between 3 to 12-months reported a standard deviation of change in ambulatory activity of around 3000 to 4000 steps per day in individuals with T2DM, prediabetes or in sedentary individuals [32, 57–59].Therefore we have anticipated a standard deviation of change of 4000 steps per day. An intervention effect of 1000 steps was considered the minimum clinically significant difference between groups and equates to around a 4 % difference in the risk of cardiovascular morbidity and mortality [13].

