### Randomisation

Once baseline data have been collected, participants are randomised (stratified by sex and ethnicity) using an online randomisation tool hosted at the University of Leicester Clinical Trials Unit. Individuals are randomised (1:1:1) to the control group, the Walking Away Group or the Walking Away Plus Group. The exception to this is individuals recruited from the same household, who are randomised to the same group. Participants are informed of their allocated treatment after baseline measures are completed. Study allocation is concealed from the study measurement teams conducting the 12-month and 48-month follow-up.

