### Data analysis

Analysis will involve two *a priori* comparisons; both intervention groups will be compared to the control group. Should any of these comparisons reveal a significant difference, then a third *a priori* comparison will be undertaken by comparing the difference between intervention groups - this will be included as a secondary analysis. Multiple linear regression analysis will be used to investigate the differences in the change in physical activity level achieved between groups at 48 months, after adjusting for potential areas of bias between groups, valid accelerometer wear time and the number of valid wear days. Analysis will be conducted on the cohort as a whole and stratified by ethnic group; interaction terms will be used to quantify the effect of ethnic group. We will also use interaction terms to assess whether the effects of the interventions are modified of gender, age, ethnicity, family history of T2DM or whether prediabetes status was confirmed at baseline; significant interactions will followed by stratified analysis. We will also assess change in physical activity at 12 months as a secondary outcome. The primary analysis will be based on analysing those with complete data at each time point in the group to which they were randomised. A sensitivity analysis will be undertaken to assess the impact of imputing missing data through multiple imputation and through a per-protocol analysis by removing those that failed to attend the initial Walking Away session in both intervention groups; per-protocol analysis for the Walking Away Plus group will be defined as removing those that that failed to attend the initial Walking Away session OR those that failed to register for or actively stopped their text messaging support via the STOP function within the first 2 months.

Analysis of secondary biochemical and anthropometric outcomes will be analysed using the same strategy and at the same time-points as that described for the primary outcome. Differentials in the time to T2DM between groups will be plotted using the Kaplan–Meier method for comparing survival curves; the log rank test will be used to assess for differences between the groups.

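### The only multiplicity rule stated for the two primary comparisons is an equal split to alpha 0.025; it is valid, but a Holm step-down gives more power at the same 5% family-wise error and the same sample size

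*Protocol article*

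**What the plan says.** The protocol article's Sample size section (Primary outcome) takes "alpha = 0.025 (allowing for 2 a priori comparisons against control conditions", with 80% power, and states "we have anticipated a standard deviation of change of 4000 steps per day". The target is "to detect a 1000 steps/day difference in change in ambulatory activity" between the intervention groups and control. With "a drop-out of 30" per cent, the result is "we require 436 per group (1308 in total").

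Under Randomisation, "Individuals are randomised (1:1:1) to the control group, the Walking Away Group or the Walking Away Plus Group".

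Under Data analysis, "both intervention groups will be compared to the control group". A third comparison, between the two interventions, is secondary and is run only if one of the first two is significant. That section gives no significance threshold, no order of testing and no step-down for the two primary comparisons. The value 0.025 appears again in the power statements for the South Asian subgroup and for secondary outcomes.

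**The concern.** There are two null hypotheses. Once one is rejected at 0.025, only one remains, and it can be tested at the full 0.05 with family-wise error still at or below 5%. This is Holm's procedure, and it holds whatever the dependence between the two tests. Holm rejects everything that the equal split rejects, and sometimes more.

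The aims include judging the intervention at two levels of intensity, so the result for each arm matters. Under a fixed split, suppose one programme succeeds and the other has p = 0.03. The second would be reported as not significant, although a 5% family-wise rate allows it to be declared effective.

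**Working it through.** **Inputs.** From Sample size: alpha 0.025 per comparison, power 0.80, SD of change 4000, difference 1000 steps/day, drop-out 30%, 436 per group. From Randomisation: 1:1:1 allocation. Two-sided testing is not stated. It is inferred because it reproduces the sample size.

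**Reproducing the stated size.**
- n per arm = 2 × [(2.2414 + 0.8416) × 4000/1000]² = 304.2, so 305 evaluable.
- 305/0.70 = 435.7, so 436 per group and 3 × 436 = 1308 in total. This matches exactly.
- One-sided 0.025 would replace 2.2414 by 1.9600 and give 251.2, so 252 evaluable and 252/0.70 = 360 per group. That does not match.

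**Set-up for the comparison of procedures.**
- Standard error of each contrast = 4000 × √(2/305) = 323.9 steps/day.
- Non-centrality for 1000 steps/day = 1000/323.9 = 3.087.
- The shared control arm with equal allocation gives a correlation of 0.5 between the two test statistics.
- Critical values: 2.241 (two-sided 0.025) and 1.960 (two-sided 0.05).
- Fixed split, both significant: P(both |Z| > 2.241).
- Holm, both significant: P(larger |Z| > 2.241 and smaller |Z| > 1.960).

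The probabilities come from the bivariate normal distribution. The two both-significant figures were also checked with 2,000,000 simulated pairs (0.689 and 0.780).

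| Quantity | Fixed 0.025 | Holm |
|---|---|---|
| Power per comparison, 1000 steps in both arms | 80.1% | 84.7% |
| Power to show both, 1000 steps in both arms | 68.9% | 78.0% |
| Power for at least one, 1000 steps in both arms | 91.4% | 91.4% |
| Power for the weaker arm, effects 1000 and 700 | 46.8% | 56.0% |
| Family-wise error, no effect in either arm | 4.6% | 4.6% |
| False positive for an inert arm, other arm 1000 steps | 2.5% | 4.2% |

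The Holm figure per comparison can be checked from its parts. The two arms have equal effects, so it is the average of the at-least-one and both probabilities: (91.4% + 78.0%)/2 = 84.7%.

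**Size of the gain.** Per comparison it is 84.7 − 80.1 = 4.6 percentage points. For both it is 78.0 − 68.9 = 9.1 points. So about 9 trials in 100 would show both programmes effective under Holm but only one under the split.

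**The case against.** The strongest reply is that nothing here is wrong. An equal split is a valid procedure, the sample size is correct, and the promised 80% is per comparison, which the design delivers. The article promises no joint power. All of that stands, and a reader who inferred from the 68.9% that the trial is underpowered, or needs more participants, would be mistaken.

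A reader might also infer that the article commits the final tests to a fixed 0.025. It does not quite say so. The figure is given as an input to the power calculations, and Data analysis states no threshold. Sizing at 0.025 is compatible with Holm, whose first step uses that level, and an analysis plan that is not shown may contain a step-down. A fixed split is the natural reading, no more.

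The gain is not free either. If one programme works and the other does nothing, the risk of declaring the inert one effective rises from 2.5% to about 4.2%. That stays within the 5% family-wise limit, but it should be disclosed in a trial of two intensities. The split also pairs each test with a simple confidence interval, which Holm does not. The article states no interval level for the primary outcome, so no particular interval can be treated as already planned.

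Finally, the correlation of 0.5 is no argument for Holm, which ignores it just as the split does. Step-down Dunnett does use it, with a first critical value of 2.212 instead of 2.241. With 1000 steps in both arms it adds little: about 85.0% per comparison and about 78% for both, with 5.0% family-wise error when neither arm has an effect.

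**Conclusion.** The point holds as an inexpensive improvement. The stated split controls error and supports the stated sample size, but Holm dominates it for testing: it makes every rejection that the split makes, keeps family-wise error at or below 5%, and needs no extra participants. It does not improve the chance of at least one success.

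The sizes rest on 305 evaluable per arm (exactly 30% drop-out), SD 4000, two-sided tests and a true effect of 1000 steps/day in both arms. With unequal effects of 1000 and 700, the weaker arm gains 56.0 − 46.8 = 9.2 points. The point falls away if the analysis plan already specifies a step-down.

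**What to change.** Before database lock, add to Data analysis, unless the analysis plan already says so: the smaller of the two p values for comparison with control is tested at 0.025 and, if it is significant, the other is tested at 0.05, both two-sided; if the smaller is not significant, neither is declared significant. Step-down Dunnett is an acceptable alternative if the shared control arm is to be used, with its own critical value stated.

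Keep the sample size. Specify the confidence level of the reported intervals, and note that an interval may not agree with the Holm decision for the second comparison. Record that the false-positive risk for an inert programme beside an effective one rises from 2.5% to about 4.2%. The cost is a few sentences and no change to the conduct of the trial.
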